## Abstract

Homes in which families are experiencing stressful and challenging circumstances can foster a social space that engenders violent behaviours in parents, inadequate childcare, and the exposure of children to criminal and antisocial behaviours at an early age in addition to many other negative social and health consequences throughout their development. Family Skills Training offers a combination of parenting knowledge, skill building, competency enhancement, and support to strengthen family protective factors, such as communication, trust, problem-solving skills, and conflict resolution. Through over a decade-long experience piloting evidence-based family skills packages globally, we developed a universal open-source family skills package, “Family UNited” (FU), designed for families with children aged 8 to 15 years living in low- and middle-income countries (LMIC). The current study aims to explore the efficacy, fidelity, and acceptability of FU in Trentino and Parma, Italy. We plan to conduct a multi-site, non-blinded, two-armed, cluster-randomised controlled trial to assess efficacy in 160 families: the intervention group receiving FU and the waitlist/control group only receiving FU after the completion of all data collection points. We will prospectively collect outcome data, assessing changes in parenting skills and family adjustment in caregivers, children’s behaviour, resilience capacities, and attitudes towards peer violence. To assess programme delivery, fidelity, feasibility, and acceptability we will include an embedded process evaluation. This study aims to evaluate the improvement in parenting skills, child well-being, and family mental health after participation in FU, compared to no intervention. Even though this trial is to be conducted in a high-income country, such results complement the existing piloting experience in LMIC. with impact-related measures encouraging the adoption of such approaches globally and beyond the EU borders.

## 1. Introduction

### 1.1. Background and Rationale

Family Skills Training offers a combination of parenting knowledge, skill building, competency enhancement, and support [1]. Family skills packages have been designed to reduce current family relationship problems and prevent future difficulties through training, support, or education [2]. They aim to strengthen family protective factors, such as communication, trust, problem-solving skills, and conflict resolution, and often include opportunities for parents and children to spend positive time together as a way to strengthen the bonding and attachment between the two.

Family skills training programmes have frequently been used at a universal level of prevention. As such, they target whole populations, most frequently through schools, neighbourhoods, or communities, without specific screening at the individual level for the level of risk presented. Such universal approaches share the assumption that almost anyone can benefit from such a prevention and health promotion/orientation package, and that delivery to groups made up of families with differing levels of risk is likely to foster engagement. Such an approach also has the potential of reducing any potential stigmatization of the programme, in the sense of associating it with targeting families with specific problems and facilitating as many families as possible to benefit from it. Nevertheless, such a universal approach does not necessarily mean that the package affects all families equivalently; but, the aim is always to mostly benefit those families facing higher levels of challenges. Individual cases with higher levels of problems will be identified by facilitators and referred to more tailored or individualised services [3].

### 1.2. The Role of the Family in Violence and Substance-Use Prevention

Homes in which families are experiencing stressful and challenging circumstances can foster a social space that engenders violent behaviours in parents, inadequate childcare, and the exposure of children to criminal and anti-social behaviours at an early age in addition to many other negative social and health consequences throughout their development. When parents are harsh in discipline and low in responsiveness, this accelerates the negative behaviours of the youth and serves as an impetus for criminal behaviours and gang involvement; whereas, warmth and positive parenting can prevent negative social outcomes, such as the initiation of drug use and other risky behaviours [4,5].

### 1.3. The Family UNited Programme

Through its over a decade-long experience piloting evidence-based family skills packages globally, the United Nations Office on Drugs and Crime (UNODC) has identified that very few family skills programmes were designed to serve the needs of families living in low-resource settings (the primary targets settings of UNODC) [6]. Nevertheless, the few available current reports appear promising and indicate the feasibility of this approach in such settings [7]. Based on this knowledge, the UNODC Prevention Treatment and Rehabilitation Section (PTRS) initiated open-sourced family skills packages designed for low- and middle-income countries (LMIC) to protect youth from vulnerabilities. The UNODC’s first experience was with the Strong Families programme, which was targeted to families living in challenged and humanitarian settings. The feasibility and impact of Strong Families have been demonstrated in families living in three cities in Afghanistan [8], in families residing in refugee reception centres in Serbia [9], and, most recently, through a multi-site randomised controlled trial in Iran [10]. It is currently being implemented in a number of other countries globally.

With the evolving experiences with Strong Families, the Families UNited programme began taking shape. Family UNited draws from three overarching theories which shaped the components of the programme sessions. Firstly, the Biopsychosocial Vulnerability Model [11] suggests that positive family coping skills, such as conflict resolution, active problem-solving skills, and positive communication, shield individual family members and protect youth from vulnerabilities stemming from the negative effects of family conflicts. In this theory, caregivers’ influence on their children is greatest when the children are younger and decreases significantly as they enter early adolescence. The second theory is the Resiliency Model [12], which emphasises the foundational role caregivers in a family play in children developing resilience. Resilience is defined as the ability to rebound from difficult or adverse circumstances [13] and is thought to be more likely to develop in children when raised in a family environment in which caregivers are both positive and supportive [14]. This theory focuses on life skills that are promoted when caregivers are supportive, such as reflective skills, emotional management skills, and the ability to problem solve. This theory is supported by research that identifies that the relationship a child has with their caregiver can have a more significant impact on their mental health trajectory than the experiences of war and displacement [15]. The third theory is the Social Learning Theory [16], which proposes that children’s daily experiences of the world through their interactions with others, imitation, and the reinforcement they receive, shape their behaviour both directly and indirectly [17]. This places the role of caregivers as pivotal for their healthy social development and also guides family skills interventions to focus on improving the quality of parenting by improving foundational parenting skills [18].

Based on its theoretical foundations, the content of the Family UNited Programme focuses on enhancing an empathetic and warm approach to caregiving; improving family cohesion, communication, and relationships; and gaining skills for emotional regulation and assertive skills for managing peer pressure. There is no content addressing substance use explicitly.

Family UNited is a universal prevention intervention designed for families with children aged between 8 and 15 years with the aim of improving parenting skills, child well-being, and family mental health.

A logic model based on this approach is shown in Figure 1 [19].

Overall, the Family UNited Programme consists of four sessions (one per week) addressing the essential core needs of parenting skills. Each session does not exceed two hours, with the first hour addressing caregivers and children separately and the second hour working with the whole families (Table 1).

So far, Family UNited has been piloted in Bangladesh and Indonesia, with promising results regarding child mental health, resilience, and parenting skills (data have been submitted for peer-reviewed publication). In addition, facilitators have been trained (remotely) in Karakalpakstan (Uzbekistan); and, an online training platform for facilitator training is being developed. Further piloting studies with families have so far had to be postponed due to COVID-19 social distancing measures in many countries.

Being a universal, evidence-informed family skills package with an overall design vision that is deemed easy to implement in low-resource settings also gives Family UNited the advantage of the ease of scalability in low- as well as higher-resource settings. It is in that context that researchers from the University of Parma and Trento were interested in piloting this package in their respective locals. To our knowledge, no other family skills programmes have been implemented in Parma or Trentino before.

### 1.4. Objectives of This Study

The current study aims to explore the efficacy, fidelity, and acceptability of this universal prevention programme with families in Trentino and Parma, Italy and investigate the feasibility of delivering the programme.

The primary objective (impact evaluation) will be to test the efficacy of the Family UNited programme in improving family-skills outcomes and caregiver and child mental health and resilience, as reported by caregivers and children, when implemented in Trentino and Parma, Italy. According to the logic model of Family UNited (Figure 1), the short-term participant and family impact will be measured and compared against a waitlist/control group.

The secondary objective (process evaluation) will be to calculate the extent of families’ attendance to Family UNited sessions to evaluate the completeness of programme delivery. Further, the fidelity will be assessed to ensure facilitator compliance with the programme, as trained.

The tertiary objective will be to explore the cultural and contextual acceptability of the Family UNited programme for families in Trentino and Parma, Italy.

### 1.5. Trial Design

To explore feasibility and ensure adequate implementation modalities, a pilot study was conducted in March/April 2022.

Subsequently, we plan to conduct a multi-site, non-blinded, 1:1 cluster-randomised controlled trial (cRCT) with two arms used to assess efficacy: the (1) intervention group (receiving the Family United programme) and (2) waitlist/control group (families only receiving the Family UNited programme after the completion of all data collection points).

We will prospectively collect all outcome data, assessing changes in parenting skills and family adjustment in caregivers, children’s behaviour, resilience capacities, and attitudes towards peer violence.

To assess programme delivery, fidelity, feasibility, and acceptability, we aim to include an embedded process evaluation.

## 2. Materials and Methods

### 2.1. Study Setting

This study will take place in different schools in Parma city and Trento province, Italy. The exact location will be decided by the Italian researchers of this study after conducting local assessments for the suitability of the location. Parma city has a population of 194,417; whereas, 538,223 persons live in the Trento province. Parma and Trento are two rich cities in the Italian national scene, located in two of the wealthiest and most-developed regions of Italy, Emilia-Romagna and Trentino-Aldo Adige, with a GDP per capita of 33.6 and 36.9 (in thousand EUR), respectively [20]. In both cities, there are problems of youth addiction due to a number of possible reasons, including the social disintegration of a large number of immigrants, including second-generation immigrants [21]. In their study, Deolmi et al. indicate that 31% of the participants with mental disorders, which includes drug use and addiction, are of immigrant origins [21]. This could be partly explained by the difficulties in integration faced by immigrants when settling down in host countries [22].

### 2.2. Eligibility Criteria

Participants will be parents or caregivers and one child under their care aged between 8 and 15 years. Sampling will be opportunistic, using a ‘universal’ approach in which facilitators will recruit families from the general population, not targeting specifically those with particular difficulties or risks. The inclusion criteria are caregivers who speak Italian and have at least one child under their care, aged 8 to 15 years, willing to take part in the programme and those in the area for the duration of the whole study. Families who took part in any other family skills training programme in the past 24 months, or where the caregiver lives separately from the child or does not have a constant relationship of attendance with the child (i.e., less than half of the time in cases of shared custody), will be excluded from this study.

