Facilitators in both Trentino and Parma have been trained on Family UNited through 3 full-day in-person workshop in December 2021. They reached pilot families in March/April 2022 and implemented the programme. The same facilitators will implement Family UNited during the planned cRCT.

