### 2.4. Waitlist/Control Condition

Participants allocated to the waitlist/control group will only receive the questionnaires at the same time as the families in the intervention group. They will not receive any family skills intervention, nor will any contact be made with facilitators before all data have been collected. Only then the waitlist/control families will start the Family UNited training programme, as shown in Figure 2.

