**Figure 3 ijerph-20-06548-f003:**
[figure not shown]
Data collection scheme.

**Table 1 ijerph-20-06548-t001:** Family UNited structure [19].

	Caregiver Session	Child Session	Family Session
**Week 1**	Understanding praising and encouraging children	Building positive qualities	Our family’s positive qualities
**Week 2**	Changing challenging behaviour	Handling stress	Learning about each other
**Week 3**	Responding to un-desirable behaviour	Skills to resist peer pressure I	Understanding peer pressure and family connections I
**Week 4**	Communicating and taking care of yourself	Skills to resist peer pressure II	Understanding peer pressure and family connections II

**Table 2 ijerph-20-06548-t002:** Dummy table of process evaluation components, data sources, and indicators.

Process Evaluation Component	Data Source	Indicator	Caregiver				Child				Family				Total
			Session 1	Session 2	Session 3	Session 4	Session 1	Session 2	Session 3	Session 4	Session 1	Session 2	Session 3	Session 4	
Dose delivered	Coordinator	Number of sessions delivered													
Fidelity	Observer	Percentage of activities reported as covered													
	Facilitator	Percentage of activities reported as fully/mostly covered as 3/4 (on a scale of 1 [not/hardly] to 4 [fully])													
	Observer	Percentage of programmes with ≥2 facilitators at every session													
	Observer	Percentage of programmes with ≥1 of the same facilitators at every session													
	Observer	Percentage of programmes with >4 and <15 families													
Dose received	Facilitator	Percentage of activities reporting interest of young people; and parents/carers as 3/4 (on a scale of 1 [low] to 4 [high])													
Reach	Observer	Percentage of families attending all 4 sessions													
Inputs	Observer	Percentage of sheets with a good or very good evaluation of the quality of childcare and travel arrangements													
	Observer	Percentage of sheets with a positive evaluation of (area of) refreshments													
	Observer	Percentage of sheets with a positive evaluation of room/materials/equipment													

**Table 3 ijerph-20-06548-t003:** Timeline of the pilot study and RCT.

Week	Activity
	PILOT STUDY
Week 1	Recruitment of 2 Research Assistants and training on measure completion
Week 2	Research Assistants recruit 10 families.
Week 2	Research Assistants conduct baseline measures and consent (Time 1) with all 10 families

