Week 3–6	Families take part in weekly sessions of Family UNited for 4 weeks
Week 6	All families’ complete measures again (Time 2)
	RCT
Week 1–2	Research Assistants assess families for eligibility and inform them about the planned trial and the programme verbally and in writing
Week 3	Research Assistants recruit 160 families, obtain written assent/consent and conduct baseline measures (Time 1; pre-intervention) with all families After data collection has been completed, families are randomly allocated to intervention or control group
Week 4–7	Intervention group families take part in weekly sessions of Family UNited for 4 weeks Facilitators and observers complete process evaluation tools after each session
Week 9	ALL families complete measures again (Time 2; post-intervention). 10 caregivers from the intervention group are interviewed for acceptability
Week 13	ALL families complete measures again (Time 3; follow-up)
Week 14–17	Control families take part in weekly sessions of Family UNited for 4 weeks

**Table 4 ijerph-20-06548-t004:** Sample size estimates based on selected (statistically significant in paired *t*-test *) results from the pilot trial for Family UNited in Parma and Trentino, Italy, in spring 2022 [25].

	Before: Mean ± SD	After: Mean ± SD	Paired Difference in Means ± SD	Sample Size (Power)	
PAFAS				80%	90%
Positive encouragement (*n* = 14)	5.1 ± 2.3	2,1 ± 1.2	3.0 * ± 2.7	**10**	**12**
Parental adjustment (*n* = 14)	5.9 ± 3.1	4.7 ± 2.7	1.2 ± 2.7	**40**	**54**
Family relationships (*n* = 14)	3.8 ± 2.3	2.9 ± 1.7	0.9 * ± 1.2	**17**	**21**
SDQ					
Hyperactivity (*n* = 14)	2.8 ± 2.1	2.1 ± 1.8	0.7 * ± 1.1	**23**	**30**
Conduct problems (*n* = 14)	2.6 ± 1.8	1.3 ± 1.1	1.4 * ± 1.4	**12**	**15**
Total Difficulty Scale (*n* = 14)	10.9 ± 5.0	8.4 ± 4.4	2.6 * ± 3.7	**20**	**26**
CYRM-R					
Total CYRM (*n* = 12)	58.8 ± 19.0	60.8 ± 18.2	1.9 ± 6.9	**104**	**138**
Personal resilience (*n* = 12)	35.8 ± 11.8	37.4 ± 11.3	1.7 ± 3.9	**45**	**61**

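### Section 2.2 has the programme's facilitators recruit families, Table 3 has research assistants do it, and section 2.4 does not say when its ban on facilitator contact begins

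*Protocol article*

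**What the plan says.** Protocol article, section 2.2 (Eligibility Criteria), describes the sampling and the recruiter together: "Sampling will be opportunistic, using a ‘universal’ approach", in which "facilitators will recruit families from the general population". Section 2.3 (Intervention Condition) identifies the facilitators as the trained people who ran the pilot and adds: "The same facilitators will implement Family UNited during the planned cRCT".

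Table 3 assigns the work to a different role. In RCT weeks 1–2, "Research Assistants assess families for eligibility and inform them about the planned trial". In week 3, "Research Assistants recruit 160 families, obtain written assent/consent and conduct baseline measures". The pilot rows match: "Research Assistants recruit 10 families".

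Section 2.4 (Waitlist/Control Condition) says: "Participants allocated to the waitlist/control group will only receive the questionnaires" on the same schedule as the intervention families, "nor will any contact be made with facilitators before all data have been collected".

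Section 2.8 (Recruitment of Families) lists channels and does not say who recruits. Section 2.9 (Allocation) says that schools are the randomised units, acknowledges that randomising ahead of recruitment can affect recruitment and dropout in the control arm, and responds by telling staff to withhold the allocation from families until consent and baseline are complete.

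**The concern.** The article gives two incompatible answers to who recruits, and a site could follow either. The difference matters because of the design. In a cluster trial that recruits after the clusters are randomised, randomisation does not protect the choice of which families are approached. Opportunistic sampling leaves that choice to the recruiter. If the recruiter will also run the groups and knows which schools are in the intervention arm, the families approached, or the effort spent on them, may differ between arms. The trial is openly unblinded after baseline and its outcomes are questionnaires completed by caregivers and children, so any difference in the kind of family recruited would pass directly into the comparison. A larger sample would not remove it.

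The no-contact rule in section 2.4 adds a second ambiguity. If facilitators do recruit in control schools, whether that contact is permitted depends on when the rule starts, and the article does not say.

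**Working it through.** The point concerns roles and timing, and the plan attaches no figure to it, so there is nothing to recalculate. The check sets the sections side by side.

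1. **Who recruits.** Section 2.2: facilitators. Table 3, RCT rows: research assistants, for screening, information, recruitment, consent and baseline, covering all 160 families. Section 2.8: channels only. No section says which of the two statements prevails.

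2. **Are these different people?** Yes, by function. Section 2.3 has facilitators deliver the sessions. Table 3 has research assistants take the measures. No text equates the two roles.

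3. **Is it a one-word slip?** It may not be. Section 2.3 says that facilitators reached the pilot families, while the pilot rows of Table 3 have research assistants recruit them. Section 2.10 asks facilitators to report on recruitment in their reflection sheets. Some facilitator role in recruitment is therefore plausible in practice.

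4. **When is the arm fixed?** Section 2.9 has schools randomised and speaks of randomisation before recruitment. Table 3 places the allocation of families after baseline. The two fit together if the school's arm is drawn first and the family is told after baseline. On that reading a control-school family is in effect in the control arm when it is first approached.

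5. **When does the no-contact rule begin?** Section 2.4 covers participants allocated to control.
   - If the rule runs from school randomisation, a facilitator recruiting in a control school contravenes it.
   - If it runs from the moment the family learns its allocation, a recruitment contact comes earlier and is allowed.
   - The text supports either start.

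6. **What does the safeguard cover?** Section 2.9 restricts what staff tell families. It does not say that recruiters are unaware of the school's arm, or that the same people recruit in both arms.

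7. **Consequence under each version.** If Table 3 governs, programme deliverers do not select families and this particular risk does not arise. If section 2.2 governs, they do, after the school's arm is fixed, and nothing stated prevents them from knowing it.

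**The case against.** The strongest reply is that the two statements describe a divided task: facilitators help publicise the programme and reach families, while research assistants screen, obtain consent and measure. The pilot is described in both ways, and section 2.8 relies mostly on open channels such as advertising, schools, parent groups and public notices, to which families respond themselves. This is plausible, but the article never says it, and section 2.2 uses the word recruit without qualification. The contradiction stands.

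A reader might go further and infer three things that the documents do not support.

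- **That the control condition is already breached.** The rule in section 2.4 can be read as starting at allocation, and a recruitment conversation is not exposure to the programme. What stands is that the start is undefined.
- **That facilitators recruit in intervention schools and research assistants in control schools.** No section says so, and Table 3 gives research assistants every family.
- **That the deliverers choose the families whichever section is followed.** Under Table 3 they do not.

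It is also fair to say that opportunistic, universal sampling is declared openly and is not itself a defect, and that section 2.9 acknowledges the hazard of recruiting after randomisation. Its remedy concerns disclosure to families, so it answers the point only in part.

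**Conclusion.** The contradiction between section 2.2 and Table 3 is real and unresolved, and section 2.4 leaves the start of its contact rule open. Following section 2.2 as written would let those who deliver the programme recruit opportunistically once schools are randomised, which leaves a risk of differential recruitment by arm.

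That risk is an inference from the design; the article reports no such difference. Its size cannot be derived from the document, and it may be zero if the same people recruit in both arms. The conclusion assumes that schools are randomised before families are approached, as section 2.9 implies. If the draw took place only after baseline, recruiters could not know the arm and this route would close. The point deserves correction because it bears on internal validity and is cheap to settle.

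**What to change.** - **Section 2.2:** name research assistants as recruiters, as Table 3 already does, for schools in both arms and with the same scripted invitation. Where feasible, keep them unaware of the school's allocation until baseline is complete.
- **Section 2.4:** state that the rule against facilitator contact covers the recruitment period.
- **Trial report:** section 4 says that the trial has begun, so report who recruited in each school and whether they knew its allocation. Readers can then judge the risk for families already enrolled.

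Table 3 already gives this work to research assistants, so no extra staff are needed. The small downside is losing facilitators' personal networks as an invitation channel. If facilitators have in fact been recruiting, the change alters conduct as well as wording, and the recruitment item on their reflection sheets would need to be reworded.

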### 2.3. Intervention Condition

Family UNited will be delivered to families in groups of approximately 12 families. Only one or two parents or main caregivers will be invited to attend, with a maximum of two children under their care aged 8 to 15 years.

The programme consists of four meetings (Table 1) spread over four weeks. In the first hour of each week, two facilitators will work with caregivers in one room; whereas, the other two facilitators will work with the children in a separate room. In the second hour of the meeting, all four facilitators and all caregivers and children will come together in one room for the joint family session.

During the caregiver sessions, caregivers will learn about children’s behaviour and how caregiver attention changes children’s behaviour. They will learn techniques to make the behaviour they want to see more likely to happen. They will practice how to communicate with their children in a way that is healthy and promotes listening. They will also be shown ways to make sure their children know that they are loved and, at the same time, how to set limits that help the children stay safe and feel secure.

During the child sessions, children will learn about some good ways to deal with stress and the importance of talking to trusted adults about their feelings. They will think about their caregiver’s responsibilities and have discussions about the positive qualities they want to develop and use as adults. In addition, children will learn and practice ways to deal with peer pressure situations, increasing the likelihood that they will stay healthy and safe.

In the family sessions, caregivers and their children will come together to practice positive and respectful communication. Together, they will play games and participate in activities that encourage positive relationships and build trust. The children will enjoy one-to-one time with their caregivers while talking about the strengths and qualities they share as families and the things they can do together to demonstrate their family values.

Based on the process evaluation, we will monitor participants’ attendance at each of the sessions and calculate the “Reach” and “Dose received”, as shown in Table 2.

During the trial period, participants will be requested not to take part in any other family skills programme, nor will any other contacts be made with the families, apart from the scheduled sessions of the Family UNited programme.

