### 2.7. Sample Size

In the pilot study, 26 caregivers (17 in Parma and 9 in Trentino) completed the data collection before the intervention; whereas, only 18 caregivers (11 in Parma and 7 in Trentino) completed the data collection 2 weeks after the intervention. Overall, 19 children (11 in Parma and 8 in Trentino) completed both data collections. Based on the completion of both time points and excluding missing data, the following sample sizes were estimated. To keep the power at 80%, and to be able to show results for each of the scales, the sample size was calculated to be 40 participants in each group, resulting in a total number of families of 160, as shown in Table 4 and Figure 2.

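### The prior-training exclusion covers only other programmes, so families trained in Family UNited in the 2022 pilot stay eligible; the effect is conditional and probably small

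*Protocol article*

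**What the plan says.** All references are to the protocol article.

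- **Section 2.2 (eligibility)** excludes "Families who took part in any other family skills training programme in the past 24 months". It gives no exclusion for having already received Family UNited, and none appears elsewhere in the article.
- **Section 2.3 (intervention)** states that during the trial "participants will be requested not to take part in any other family skills programme". These are families being offered Family UNited, so *other* here means other than Family UNited.
- **Section 1.3 (programme)** says "To our knowledge, no other family skills programmes have been implemented in Parma or Trentino before". Family UNited had itself been piloted there, so the word carries the same meaning.
- **Section 1.5 (design)** states that "a pilot study was conducted in March/April 2022". Of the facilitators in both areas, Section 2.3 says "They reached pilot families in March/April 2022 and implemented the programme. The same facilitators will implement Family UNited during the planned cRCT".
- **Section 2.7 (sample size)** reports: "In the pilot study, 26 caregivers (17 in Parma and 9 in Trentino) completed the data collection before the intervention". Table 3 lists 10 families for the pilot.
- **Section 6** dates the protocol 17 November 2022, and **Section 4** says the trial has started.

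**The concern.** The authors judged that family skills training within 24 months makes a family unsuitable. The one such training they document in their own areas is their pilot, seven to eight months before the protocol date and so well inside the window. Taken literally, the criterion screens for programmes that the authors believe have not run locally and lets through the one that has.

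Two things are at stake. A pilot family allocated to the intervention repeats content it has already had. Its baseline may already be improved, and its further change is likely to be smaller. A pilot family on the waitlist is not untreated, although the Abstract describes the comparison as one with no intervention.

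**Working it through.** **1. Does the wording reach pilot families?** In Sections 1.3 and 2.3 the contrast is between Family UNited and everything else. Carried into Section 2.2, the same meaning leaves Family UNited outside the exclusion. A 24-month look-back from any date up to March/April 2024 would include the pilot, so the wording and not the window leaves these families in.

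**2. The plan's own figure.** The 40 per group in Section 2.7 matches the Parental adjustment row of Table 4 (paired difference 1.2, SD 2.7, 80% power). With two-sided alpha 0.05 (two-sided is assumed), the paired normal formula gives

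n = ((1.960 + 0.842) × 2.7 / 1.2)² = 39.7, rounded up to 40.

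At 90% power it gives 54, also as stated. The total of 160 follows if a group means one arm at one site (4 × 40). That is an assumption, because Figure 2 is not shown. I take 80 families per arm below.

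**3. How dilution arises.** Let δ be the true effect on change and f the share of families with prior exposure, equal in both arms. Suppose exposed families keep their pilot gain and gain nothing more, and unexposed controls do not change. Under the time-by-group analysis in Section 2.11.3:

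- mean change, intervention arm: (1 − f)δ + f × 0 = (1 − f)δ
- mean change, waitlist arm: 0, whether exposed or not
- contrast: (1 − f)δ

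The loss therefore comes from the intervention arm and is counted once. Exposed controls mostly shift baseline and follow-up together.

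**4. Ceiling on f.** The number of pilot families is not stated. I take 10 (Table 3) to 26 (one family per baseline caregiver) and suppose that all of them enrol.

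**5. Effect on power.** The standard error of a difference between two arms of 80 is 2.7 × √(2/80) = 0.427. This takes 2.7 as the SD of change in each arm and applies no design effect for clustering.

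| Pilot families enrolled | f | Contrast | Power | Needed per arm for 80% |
|---|---|---|---|---|
| 0 | 0 | 1.200 | 80.3% | 80 |
| 10 | 10/160 = 6.25% | 1.125 | 75.0% | 91 |
| 26 | 26/160 = 16.25% | 1.005 | 65.3% | 114 |

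A design effect would lower every power figure. If only one to three families enrolled, f would be 1/160 = 0.6% to 3/160 = 1.9%.

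**The case against.** The strongest reply is that the harm may never occur. No section says that a pilot family will be enrolled. Recruitment runs through schools, adverts, municipal notices and social networks (Section 2.8) in areas of 194,417 and 538,223 people (Section 2.1). Table 3 sets out separate recruitment for pilot and trial. Section 2.2 has facilitators recruiting and Table 3 has research assistants doing so; in either case, staff who ran a small pilot could recognise its families. This stands, and it is why the table in the working is a ceiling.

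The ceiling is generous in other ways too. The 26 are caregivers, and Section 2.3 allows one or two per family. Zero further gain is a worst case. Section 2.12.7 reports only that some families have wished for additional sessions, and it says so in the context of add-on modules, so it is weak evidence of re-enrolment. The exclusion is also not empty: Section 1.3 is qualified as being to the authors' knowledge, and families may have been trained elsewhere.

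A reader might infer that pilot families in both arms each pull the contrast towards zero. Under the planned analysis they do not, for the reason in step 3. What is lost on the waitlist side is the clean description of an untreated comparator.

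It can also be said that the intent is obvious, or that screening of pilot families is a detail for the full protocol. The article does state the criterion, though, and its wording leaves out the exposure nearest to hand. That part is not answered.

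**Conclusion.** The point holds as a wording gap of minor severity. As written, and read consistently with Sections 1.3 and 2.3, the exclusion leaves 2022 pilot families eligible.

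Its effect depends on whether any enrol, which the article neither states nor rules out. The ceiling is a 6% to 16% smaller contrast, resting on three assumptions: all 10 to 26 pilot families enrol, they are spread evenly over the arms, and they gain nothing further. The likely effect is much smaller and may be zero. The stronger inference, that the trial's contrast is in fact diluted by pilot families, is not supported.

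**What to change.** Reword the exclusion in Section 2.2 to cover any family skills training programme, including Family UNited (for example the 2022 pilot), in the past 24 months.

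Because the trial has started, identify enrolled families with prior participation. Use pilot records if they are still held; otherwise ask families directly. Asking may be needed, since Section 2.11.1 keeps names off electronic files and has paper identifier sheets destroyed at study end, and the pilot may have been handled the same way. Then repeat the main analysis without any such families as a sensitivity analysis, and report how many there were, by arm.

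The cost is a one-line change, one check or one question per family, and the loss of at most a few willing families. If no prior participants are found, a sentence saying so closes the point.
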